## Abstract

**Introduction:**

Sodium-glucose co-transporter 2 inhibitors (SGLT2i) reduce cardiovascular events across a wide range of kidney function, including advanced stages of chronic kidney disease, but evidence for their efficacy in patients with kidney failure on haemodialysis is lacking. The underlying mechanisms remain incompletely understood, and whether cardiovascular benefits depend on residual kidney function is unknown.

**Study design:**

The Dapagliflozin in Hemodialysis (DAPA-HD) trial (NCT05179668) is an academic, multicentre, randomized, double-blind, placebo-controlled trial designed to assess the cardiovascular effects of dapagliflozin in 220 patients with kidney failure receiving haemodialysis. Stratified block randomization was based on patient-reported residual urine volume. The primary endpoint is the change in left ventricular mass indexed to body surface area using echocardiography after 6 months of treatment. A prespecified subgroup analysis will compare treatment effects between patients with residual urine output >200 ml/24 h versus ≤200 ml/24 h. Secondary endpoints include additional echocardiographic assessments, changes in biomarker concentrations, quality of life, and clinical events.

**Discussion:**

The DAPA-HD trial is the first trial specifically evaluating the cardiovascular and haemodynamic effects of dapagliflozin in patients with kidney failure receiving maintenance haemodialysis with and without residual urine outputs.

## Background

Cardiovascular disease is the leading cause of death in patients with kidney failure receiving haemodialysis.^1–3^ These patients represent one of the highest risk groups for cardiovascular morbidity and mortality, particularly due to left ventricular hypertrophy, heart failure, arrhythmias, and sudden cardiac death.^2,4,5^ Effective cardiovascular-kidney risk management in chronic kidney disease (CKD) is complicated by altered pharmacokinetics, disease-specific complications (including electrolyte disturbances, volume overload, and uraemia), and limited evidence from CKD populations.

Sodium-glucose co-transporter 2 inhibitors (SGLT2i) reduce cardiovascular events across a wide range of kidney functions, including patients with an estimated glomerular filtration rate (eGFR) as low as 20 ml/min/1.73 m^2^.^6,7^ However, patients with kidney failure requiring dialysis were systematically excluded from landmark SGLT2i trials. Prior studies have demonstrated reverse cardiac remodelling with SGLT2i in populations with type 2 diabetes, left ventricular hypertrophy, or heart failure, but whether these effects persist in patients with kidney failure requiring dialysis is unclear.^8–11^ Residual kidney function among patients receiving maintenance haemodialysis varies substantially and may influence the potential cardiovascular effects of SGLT2i. While formal quantification of residual renal clearance is complex and not routinely feasible at scale, residual urine output provides a pragmatic, patient-identifiable marker that reflects ongoing kidney activity and is widely used in clinical practice.^12^

The Dapagliflozin in Hemodialysis (DAPA-HD) trial was designed to evaluate the cardiac effects of dapagliflozin in haemodialysis patients with prespecified stratification according to residual urine output as a pragmatic surrogate of residual kidney function. The trial tests the hypothesis that dapagliflozin can reduce left ventricular mass in this patient population and provides an opportunity to systematically assess the tolerability and safety of dapagliflozin in haemodialysis patients across the spectrum of residual kidney function (*Figure 1*).

**Figure 1 xvag104-F1:**
[figure not shown]
Trial design of the dapagliflozin in haemodialysis (DAPA-HD) trial. The DAPA-HD trial is an academic, investigator-initiated, multicentre, randomized, double-blind, placebo-controlled trial evaluating the effect of dapagliflozin (10 mg daily) versus placebo on the left ventricular mass indexed to body surface area using echocardiography over 6 months in patients with kidney failure receiving maintenance haemodialysis and left ventricular hypertrophy (LVH)

## Methods

### Study design and population

The DAPA-HD trial (NCT05179668) is an academic, investigator-initiated, multicentre, randomized, double-blind, placebo-controlled phase 2 trial designed to evaluate the effects of the SGLT2i dapagliflozin on cardiac structure and function in patients with kidney failure receiving maintenance haemodialysis (*Figure 1*).

Patients were eligible if they were aged ≥18 years, received maintenance haemodialysis three times weekly for ≥3 months and ≤5 years, had a body mass index <45 kg/m^2^, a stable dry weight (±5 kg during the preceding 3 months), and an interventricular septal thickness >11 mm (*Table 1*). Key exclusion criteria were type 1 diabetes mellitus, a history of diabetic ketoacidosis, scheduled living-donor kidney transplantation, severe valvular heart disease, an acute coronary syndrome within the previous 30 days, known hypersensitivity or intolerance to SGLT2i, or SGLT2i therapy within the previous 6 months.

**Table 1 xvag104-T1:** Inclusion and exclusion criteria

Inclusion criteria: Age ≥18 years Maintenance haemodialysis 3×/week for ≥ 3 months and ≤5 years BMI <45 kg/m^2^ and stable weight (±5 kg [‘dry weight’]) over the preceding 3 months Interventricular septum width >11 mm ** Exclusion criteria: ** Treatment with SGLT2i within the last 6 months Hypersensitivity or intolerance to SGLT2 inhibitors History of Type 1 diabetes mellitus History of diabetic ketoacidosis Scheduled kidney transplant from a living donor Acute coronary syndrome during the last 30 days Severe valvular heart disease Women of childbearing potential who are unwilling or unable to use an acceptable method to avoid pregnancy for the entire study (oestrogen and/or progesterone treatment). Pregnancy Breastfeeding Substance abuse Life expectancy < 1 year Other significant disease or pathology that might predispose the patient to an unacceptable risk or interferes with the study in the opinion of the investigator.

### Treatment protocol and follow-up procedures

Eligible patients were randomized 1:1 to receive either dapagliflozin 10 mg once daily or a matching placebo for 6 months, using a stratified block randomization scheme based on residual urine volume (>200 ml vs. ≤ 200 ml per 24 h). Residual urine output was assessed at study entry based on patient-reported 24-h urine volume and used as a stratification variable (>200 ml vs. ≤ 200 ml per 24 h). Randomization was performed centrally using an online tool (www.randomizer.at), and both participants and investigators remained blinded to treatment allocation. Study visits were scheduled at baseline and 6 months, with additional safety monitoring conducted at every dialysis session. These routine contacts were used to record adverse events, monitor blood chemistry (including glucose, pH, and potassium) as available according to local clinical practice, and assess drug tolerability and adherence. Echocardiographic assessments were scheduled at baseline and at 6 months and performed immediately after dialysis. Dialysis prescriptions, including ultrafiltration targets and dry weight, were determined at the discretion of the treating nephrologists in accordance with routine clinical practice.

Echocardiographic examinations were performed and analysed by a dedicated investigator (CM) with formal national certification in transthoracic echocardiography, who was blinded to treatment allocation. The same investigator conducted on-site image acquisition across participating centres and performed centralized analysis according to a standardized imaging protocol. Technically challenging cases were reviewed in conjunction with a second investigator ([name]), who is board-certified in cardiology and holds national and EACVI certification in adult transthoracic echocardiography. At external participating sites, study-specific echocardiographic acquisitions were performed using the same ultrasound system (Canon Medical Systems), which was provided free of charge for study use and transported between sites. The manufacturer had no role in study design, data acquisition, analysis, interpretation, or manuscript preparation. Left ventricular mass was calculated using two-dimensional linear measurements obtained from the parasternal long-axis view at end-diastole in accordance with current ASE/EACVI guideline recommendations, using the Devereux-modified ASE formula and indexed to body surface area. Studies deemed non-evaluable due to insufficient image quality were classified as missing for the primary endpoint.

Additional assessments included laboratory analyses with biomarker serum samples obtained from the first blood draw at the beginning of the dialysis session, as well as quality of life evaluation using the Kidney Disease Quality of Life Short Form (KDQoL-SF, German version 1.2) at baseline and 6 months.^13^

### Study objectives and endpoints

The primary endpoint of DAPA-HD is the change in left ventricular mass indexed to body surface area (LVMI), as measured by echocardiography after 6 months of treatment. Originally, the primary endpoint was defined as the change in LVMI measured by cardiac magnetic resonance imaging (cMRI). Shortly after study initiation and prior to unblinding, the primary imaging modality was changed to transthoracic echocardiography due to feasibility considerations and resource constraints inherent to an investigator-initiated trial. This protocol amendment was approved by the institutional ethics committee, and a revised sample size calculation was conducted accordingly.

Additional echocardiographic outcomes of interest include changes in left ventricular ejection fraction (LVEF), left atrial diameter, and strain analysis of the left atrium and the left and right ventricles. Additional assessments include changes in blood pressure, heart rate, metabolic parameters (including HbA1c, insulin, c-peptide, glucagon, β-hydroxybutyrate, GLP-1, cortisol, growth hormone, and pyruvate), cardiovascular biomarkers (hsTnT and NT-proBNP), and quality of life. All hospitalizations and deaths were recorded throughout the study period. Safety monitoring was conducted at each dialysis visit, with particular attention to signs of euglycemic ketoacidosis, genital infections, and electrolyte disturbances.

A key exploratory objective of the trial was to assess whether the cardiovascular effects of dapagliflozin are modified by residual urine volume. A prespecified subgroup analysis will compare treatment effects between patients with residual urine output >200 ml/24 hours versus ≤200 ml/24 h.

### Statistical considerations

A sample size of 186 patients was calculated to provide 90% power to detect a 7 g/m^2^ difference in the primary endpoint at a two-sided alpha of 0.05, assuming a standard deviation of 15 g/m^2^. Accounting for an anticipated dropout rate of 20%, the target enrolment was set at 220 patients. The primary hypothesis will be tested using an analysis of covariance, adjusting for baseline LVMI. The primary analysis will use a complete-case approach, including all patients with available baseline and 6-month LVMI measurements. To assess the robustness of findings under alternative missing data assumptions, sensitivity analyses will be conducted using (i) multiple imputation assuming data are missing at random, with imputation models including baseline LVMI, treatment assignment, residual urine output stratum, age, sex, and diabetes status; and (ii) pattern-mixture models to evaluate potential bias under missing not at random scenarios, including differential dropout due to death or clinical deterioration. The extent and pattern of missing data will be reported descriptively by treatment group. In prespecified subgroup analyses, outcomes will be tested with interaction terms in the ANCOVA model to assess effect modification. Serious adverse events and study drug discontinuations will be summarized descriptively by treatment group.

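### 220 patients with 20% dropout leave 176 evaluable, not the 186 the plan says it needs; on the printed inputs, power is then about 87% rather than 90%

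*Protocol article*

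**What the plan says.** The sample-size statement is in the protocol article under Statistical considerations. Its first step is: "A sample size of 186 patients was calculated to provide 90% power to detect a 7 g/m^2^ difference in the primary endpoint". The test level is 5%, two-sided, and the SD is taken as 15 g/m². Its second step is: "Accounting for an anticipated dropout rate of 20%, the target enrolment was set at 220 patients".

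Three other statements bear on the calculation:

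- Allocation is equal (Treatment protocol and follow-up procedures): "Eligible patients were randomized 1:1 to receive either dapagliflozin 10 mg once daily or a matching placebo for 6 months".
- The analysis model is baseline-adjusted (Statistical considerations): "The primary hypothesis will be tested using an analysis of covariance, adjusting for baseline LVMI". The same section makes the primary analysis complete-case, requiring both a baseline and a 6-month measurement.
- Current status and baseline characteristics reports that 220 patients were randomised and that enrolment is closed.

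The article does not say whether the SD of 15 is that of the change or a residual SD after baseline adjustment. It gives no baseline correlation as an input.

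**The concern.** The need for 186 evaluable patients, the 20% dropout and the target of 220 are printed together, and simple arithmetic shows that they disagree. The error runs in the unfavourable direction: at the plan's own dropout rate, fewer patients reach the primary analysis than the plan says 90% power requires.

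What is at stake is the accuracy of the stated power for the primary endpoint. With complete-case analysis, every patient without a 6-month value is lost to the primary test. The section on echocardiography also classes examinations of insufficient image quality as missing for the primary endpoint, and the article does not say whether the 20% includes them. If it does not, fewer than 176 would remain.

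**Working it through.** **Inputs, all from the protocol article.** Difference 7 g/m²; SD 15 g/m²; two-sided alpha 0.05; power 90%; 186 evaluable; dropout 20%; target 220 (Statistical considerations). Allocation 1:1 (Treatment protocol and follow-up procedures).

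**Step 1. The plan's 186.** For two equal arms, unadjusted, by normal approximation:

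N = 4 × (1.960 + 1.2816)² × (SD/difference)² = 4 × (3.2416)² × (15/7)² = 193.0

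This rounds up to 97 per arm, 194 in total. An exact noncentral-t calculation gives 98 per arm, 196 in total. So 186 does not reproduce exactly. Other settings come no closer: one-sided 0.05 at 90% power gives 158, two-sided at 85% gives 166, and two-sided at 80% gives 146.

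The gap is small in power. At 186, the standardised effect is 7 / (15 × √(4/186)) = 3.182, and power is Φ(3.182 − 1.960) = 88.9% (88.6% by t-test).

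It is also sensitive to rounding. With an SD of 14.7, which prints as 15, N = 4 × (3.2416)² × (14.7/7)² = 185.4, so 93 per arm and 186 in total.

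**Step 2. The dropout allowance.**

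| Calculation | Result |
|---|---|
| Evaluable after 20% loss: 220 × 0.80 | 176 |
| Enrolment needed to keep 186: 186 / 0.80 | 232.5, so 233 |
| Dropout that 220 can absorb: 1 − 186/220 | 15.5% |
| Incorrect inflation: 186 × 1.20 | 223.2, so 224 |

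None of these joins 186, 20% and 220. The incorrect multiplication comes near 220 but does not give it. This step involves neither the SD nor the choice of test.

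**Step 3. Power at the plan's own dropout.** At 176 evaluable and SD 15:

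- Standardised effect: 7 / (15 × √(4/176)) = 3.096.
- Power: Φ(3.096 − 1.960) = 87.2%; by noncentral t, 86.8%.
- Difference detectable with 90% power: 3.2416 × 15 × √(4/176) = 7.33 g/m²; by noncentral t, 7.37 g/m².

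**Step 4. The dropout error alone.** Suppose that 186 does give exactly 90% power, whatever variance input was used. The standardised effect at 186 is then 3.2416. At 176 it is 3.2416 × √(176/186) = 3.153, and power is Φ(3.153 − 1.960) = 88.4%. So even if the first step is accepted in full, the second costs about 1.6 points.

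**The case against.** The strongest case on the other side concerns the 186.

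- **Rounding.** The SD is printed as a whole number, and 14.7 gives 186 exactly by normal approximation.
- **Model.** The primary analysis is ANCOVA, while the check uses an unadjusted formula. If 15 is the SD of the change, adjustment multiplies the variance by (1 − r²), where r is the correlation of the modelled outcome with baseline. Then r of about √(1 − 186/193.0) = 0.19 makes 186 sufficient, and about √(1 − 176/193.0) = 0.30 makes 176 sufficient.
- **Illustration.** Assume that 15 is the SD of the change, that the variances at baseline and 6 months are equal, and that the baseline SD is the 36.7 g/m² of Table 2. The baseline-change correlation is then about −0.20, the residual SD 14.68 and the required total 186. Power at 176 is about 88 to 88.5%. That baseline SD was observed after planning, so it does not show how 186 was derived.
- **Source.** The article reports a revised calculation after the change of imaging modality. It condenses that calculation, and the missing input may be stated there.

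These arguments stand as far as they go. A reader might infer from the 194 to 196 above that 186 is simply wrong, or that the true power is 87% without qualification. The documents do not support either inference: both need an SD of exactly 15 and no gain from baseline adjustment, and the article settles neither. Equally, if 15 is already a residual SD, baseline adjustment recovers nothing further.

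None of this reconciles the second step. An unstated SD or correlation may justify 186, but it cannot make 80% of 220 equal 186.

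It is also fair to say that the shortfall is modest, that enrolment is closed, and that a neutral result would be read mainly from its confidence interval. This limits the severity but does not make the printed statement correct.

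**Conclusion.** The dropout step is wrong as printed: at 20% dropout, 220 enrolled leave 10 fewer evaluable patients than the plan says it needs. This rests on no modelling assumption.

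The size in power is conditional. With SD exactly 15 and an unadjusted comparison, it is 86.8 to 87.2% at 176, a type II error of about 13% rather than 10%. If 186 is accepted as giving 90%, it is about 88.4%. The shortfall is therefore roughly 2 to 3 points.

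That 186 itself gives about 89% at SD 15 is secondary, and an input the article does not print could close the gap. A reader might go further and infer that the trial is seriously underpowered or its primary analysis compromised. The figures do not show that: the estimand, model, type I error and data are unaffected. Severity is moderate, a correction to the stated power.

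**What to change.** Replace the sample-size sentences with a statement that agrees with itself, for example: 220 randomised; with 20% dropout, 176 evaluable; about 87% power for a 7 g/m² difference at SD 15 g/m² without baseline adjustment (90% power for 7.3 to 7.4 g/m²).

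If the calculation behind 186 used an unrounded SD, a residual SD or a baseline correlation, state that input and give the power at 176 on that basis instead. If the dropout rate actually assumed was nearer 15%, say so. In either case, say what the SD of 15 describes and whether the dropout figure includes non-evaluable echocardiograms.

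The cost is one or two sentences and a slightly less favourable stated power. No patients are added, and the analysis does not change.

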### Current status and baseline characteristics

The trial completed enrolment and randomization of 220 patients with kidney failure with or without residual urine output between October 2022 and January 2025 across nine sites in Austria. The baseline characteristics of the study population are presented in *Table 2*. Overall, the median age of the study population is 67 years (Q1–Q3: 57–75 years), 26% of participants are women, 42% have type 2 diabetes mellitus, 39 % have established coronary artery disease, and 28 % of patients have residual urine output ≤200 ml/day. Baseline echocardiography showed a mean LVMI of 138 g/m^2^ (standard deviation 37 g/m^2^) and a median LVEF of 59 % (Q1–Q3: 54%–65%) with 10% having an LVEF ≤40%; the median NT-proBNP concentration was 2911 pg/ml (Q1–Q3: 1181–7602 pg/ml).

**Table 2 xvag104-T2:** Baseline characteristics of the overall DAPA-HD trial population (N = 220)

	Overall
Age, years (median, IQR)	67 (57–75)
Female sex, *n* (%)	57 (25.9%)
BMI, kg/m^2^ (mean ± SD)	28.2 (5.1)
Type 2 diabetes, *n* (%)	92 (41.8%)
LVEF ≤40%, *n* (%)	19 (9.7%)
Atrial fibrillation, *n* (%)	27 (12.3%)
Coronary artery disease, *n* (%)	86 (39.1%)
Hypertension, *n* (%)	193 (87.7%)
Presumed primary cause of kidney failure	
Diabetes, *n* (%)	58 (26.4%)
Hypertension, *n* (%)	23 (10.5%)
Polycystic, *n* (%)	20 (9.1%)
Nephritis, *n* (%)	32 (14.5%)
Other/Unknown	87 (39.5%)
Residual urine volume ≤200 ml/day, *n* (%)	62 (28.2%)
Baseline medication:	
ACEi/ARB, *n* (%)	112 (50.1%)
Beta-blockers, *n* (%)	160 (72.7%)
Loop diuretics, *n* (%)	111 (50.5%)
Insulin, *n* (%)	42 (19.1%)
MRA, *n* (%)	12 (5.5%)
Baseline echocardiographic measurement:	
LV mass, g (mean ± SD)	266 (77.0)
LV mass index, g/m^2^ (mean ± SD)	138 (36.7)
LVEF, % (median, IQR)	59 (54–65)
NT-proBNP, pg/ml (median, IQR)	2911 (1181–7602)

Abbreviations: IQR, interquartile range; SD, standard deviation; BMI, body mass index; ACEi/ARB, angiotensin-converting enzyme inhibitor/angiotensin II receptor blocker; MRA, mineralocorticoid receptor antagonist; LV, left ventricular; NT-proBNP, N-terminal pro-B-type natriuretic peptide

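### The stated primary ANCOVA leaves out the residual-urine stratum used to randomise; if that stratum predicts LVMI change, a little power is lost, and adding it is free

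*Protocol article*

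**What the plan says.** - **Randomisation** (Treatment protocol and follow-up procedures): allocation was 1:1, "using a stratified block randomization scheme based on residual urine volume", with the cut at 200 ml per 24 h by patient report. No other stratification factor is named.
- **Primary model** (Statistical considerations): "The primary hypothesis will be tested using an analysis of covariance, adjusting for baseline LVMI". No other covariate is named.
- **Where the stratum does appear** (same section): in the multiple-imputation sensitivity analysis, "with imputation models including baseline LVMI, treatment assignment, residual urine output stratum, age, sex, and diabetes status". The prespecified subgroup analysis by residual urine output also uses it, through interaction terms added to the ANCOVA.
- **Size of the strata** (Current status and baseline characteristics): "28 % of patients have residual urine output ≤200 ml/day"; Table 2 gives 62 of 220.

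**The concern.** Stratified blocks keep the arms balanced on residual urine volume, so differences between strata add almost nothing to the true sampling variance of the treatment estimate. A model without the stratum does not know this and leaves the between-stratum variance in its residual. If the stratum is prognostic, the reported standard error exceeds the true one, the confidence interval is wider than it need be, and the test rejects less often than its nominal level.

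At stake is precision. Enrolment is closed at 220, so covariate adjustment is one of the few means left to gain any. There is also a point of coherence. A treatment-by-stratum interaction needs the stratum main effect, which the stated ANCOVA lacks. With the stratum in the primary model, the primary and subgroup models would be nested.

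**Working it through.** **Inputs from the protocol article**
- Target difference 7 g/m², SD 15 g/m², two-sided alpha 0.05, 186 patients for 90% power, 20% dropout, 220 enrolled (Statistical considerations).
- Low-urine share p = 62/220 = 0.282, so p(1−p) = 0.2024 (Table 2).

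**Assumptions**
- The SD of 15 is the residual SD after adjusting for baseline LVMI; the article does not say.
- Evaluable patients: 220 × 0.8 = 176, with the balance from the blocks carried over to them.
- ρ is the share of that residual variance explained by the stratum. The article gives no value; 5% and 10% are illustrative, and smaller values follow.
- Normal approximation throughout.

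**The plan's own figure.** n per arm = 2 × [15 × (1.960 + 1.282)/7]² = 96.5, so 97 per arm and 194 in total. The stated 186 gives 88.9% power. At 176, SE = 15 × √(4/176) = 2.261, 7/2.261 = 3.096, and power = Φ(3.096 − 1.960) = 87.2%. That shortfall is a separate sample-size matter; 87.2% serves here only as the starting point.

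**Between-stratum difference implied by ρ.** D = 15 × √(ρ/0.2024).
- ρ = 5%: D = 7.5 g/m².
- ρ = 10%: D = 10.5 g/m².

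**Formulas.** With s = √(1−ρ), the true SE under stratified blocks is 2.261 × s, while the model without the stratum reports 2.261.
- Type I error without the stratum: 2 × [1 − Φ(1.960/s)]
- Power without the stratum: Φ[(3.096 − 1.960)/s]
- Power with the stratum: Φ(3.096/s − 1.960)

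**Results at 176 evaluable**

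| ρ | D (g/m²) | Type I error without stratum | Power without | Power with | Loss (points) |
|---|---|---|---|---|---|
| 0 | 0 | 5.0% | 87.2% | 87.2% | 0 |
| 0.8% | 3 | 4.9% | 87.3% | 87.5% | 0.2 |
| 2.2% | 5 | 4.7% | 87.5% | 87.9% | 0.5 (0.46 unrounded) |
| 5% | 7.5 | 4.4% | 87.8% | 88.8% | 1.0 |
| 10% | 10.5 | 3.9% | 88.4% | 90.4% | 1.9 |

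**Patient equivalent.** This is the n at which the model without the stratum reaches the adjusted power at 176. It solves √n = √176 + (30/7) × 1.960 × (1 − s).
- ρ = 5%: √n = 13.266 + 0.213, n = 181.7, about 6 more patients.
- ρ = 10%: √n = 13.266 + 0.431, n = 187.6, about 12 more.

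The simpler 176/(1−ρ) − 176, which gives 9 and 20, overstates this: it ignores that the blocks already reduce the true variance of the unadjusted estimate.

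**Simulation check.** N = 186, stratified permuted blocks (block size 4 assumed), 10,000 runs per scenario. At D = 10 the mean model SE without the stratum was 2.20 against an empirical SD of 2.11. Type I error was 4.1%, and power was 89.6% without and 91.3% with the stratum. At D = 5, power was 89.0% and 89.4%.

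**The case against.** **The loss is conditional and probably small.** This stands. The article gives no estimate of how far residual urine volume predicts LVMI change, and the 5% and 10% shares need between-stratum differences above the 7 g/m² target effect.

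**Stratification was for effect modification, not prognosis.** This also stands. A reader might infer that the trial stratified because it expects the stratum to predict LVMI change, so that the loss is certain. Study objectives and endpoints and the Discussion ask only whether the effect of dapagliflozin depends on residual urine output. A prognostic role is plausible but not stated.

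**The imputation model is not inconsistent with the primary model.** A reader might take the stratum's presence in one and absence from the other as a contradiction. It is not. An imputation model may properly hold auxiliary predictors that the analysis model lacks, and the article does not say that the analysis model changes after imputation.

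**Validity and the planned power are unaffected.** Correct under the assumptions used here. The test errs on the conservative side. With total SD 15, the model without the stratum never falls below the power that the plan's own inputs give, because the sample size takes no credit for stratification. The loss is relative to an adjusted analysis.

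**The covariate list may be in an analysis plan not shown.** This carries less weight. The article states the primary model and names its covariate, so this is a stated choice rather than a missing detail. If a fuller plan already includes the stratum, the two texts need only be aligned.

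**Conclusion.** The point holds in conditional form and is minor. The stated primary model omits the only named stratification factor. If that factor predicts LVMI change beyond baseline, the standard error is slightly too large and the test mildly conservative. The loss is about 1.0 (1.9) power points at an assumed variance share of 5% (10%), under half a point for between-stratum differences of 3 to 5 g/m², and nil if the stratum predicts nothing. These figures rest on SD 15 as the residual SD, 176 evaluable patients and stratum balance among them. The documents do not support reading the omission as a certain loss of power or as a threat to the validity of the primary test.

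**What to change.** Before unblinding, state the primary model as LVMI at 6 months (or its change) on treatment, baseline LVMI and residual-urine stratum as randomised. Fit this same analysis model after multiple imputation, and keep the fuller imputation model, with age, sex and diabetes status, as it is. Let the subgroup model by residual urine output add only the treatment-by-stratum term.

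The cost is one line of text and one degree of freedom. No new data are needed, since the stratum was fixed at randomisation for all 220 patients.

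### The primary complete-case ANCOVA names only baseline LVMI as a covariate, leaving out the randomisation stratum and the other baseline variables in the plan's own imputation model

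*Protocol article*

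**What the plan says.** The section Statistical considerations fixes the primary model: "The primary hypothesis will be tested using an analysis of covariance, adjusting for baseline LVMI". It also fixes the analysis set: "The primary analysis will use a complete-case approach, including all patients with available baseline and 6-month LVMI measurements". No other covariate is named.

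The section Treatment protocol and follow-up procedures describes 1:1 block randomisation stratified by patient-reported urine volume (above 200 ml versus 200 ml or less per 24 h). It adds a second source of missing outcomes besides dropout: "Studies deemed non-evaluable due to insufficient image quality were classified as missing for the primary endpoint".

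Two sensitivity analyses for missing data are prespecified in Statistical considerations. One is multiple imputation under missing at random, "with imputation models including baseline LVMI, treatment assignment, residual urine output stratum, age, sex, and diabetes status". The other is "pattern-mixture models to evaluate potential bias under missing not at random scenarios, including differential dropout due to death or clinical deterioration". How much is missing, and in what pattern, will also be described for each arm.

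On expected loss: "Accounting for an anticipated dropout rate of 20%, the target enrolment was set at 220 patients".

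**The concern.** The plan uses four baseline variables when it imputes missing outcomes, and one of them also governed the randomisation. The analysis that carries the trial's conclusion uses none of the four.

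The first consequence is for precision. Stratified randomisation balances the arms on urine volume. If urine volume predicts LVMI change and is left out of the model, the variation it explains stays in the residual, and the reported standard error is somewhat larger than the design warrants.

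The second consequence is for bias. Randomisation balances the arms among everyone randomised, but not necessarily among completers. If, say, patients with diabetes leave the placebo arm more often than the dapagliflozin arm, completers differ between arms in the share with diabetes. A model that conditions only on arm and baseline LVMI attributes any resulting difference in 6-month LVMI to treatment. The variables that would remove this part of the bias are already collected.

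**Working it through.** **Inputs from the Protocol article.** Statistical considerations: target difference 7 g/m², SD 15 g/m², two-sided alpha 0.05, 220 enrolled, 20% dropout. Table 2: type 2 diabetes 41.8%, urine volume 200 ml/day or less 28.2%.

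**Assumptions, not in the document.** Dropout patterns by arm and covariate; an effect g of each covariate on 6-month LVMI, given baseline, of 5 to 15 g/m².

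**Step 1, the plan's own figure.** The article states: "A sample size of 186 patients was calculated to provide 90% power to detect a 7 g/m^2^ difference in the primary endpoint". With the inputs listed above, the usual two-sample formula gives 97 per arm, 194 in total, and 186 patients give 88.9% power. The stated 186 is therefore not reproduced. That is a separate matter and is not used below.

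**Step 2, standard error.** At 20% loss, 220 × 0.80 = 176 complete cases. SE = 15 × √(4/176) = 2.26 g/m². Power for 7 g/m² is 87%.

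**Step 3, precision lost by omitting the stratum.** The stratum explains a share p(1−p)g²/15² of the variance, with p = 0.282 and p(1−p) = 0.2025. This takes 15 g/m² as the residual SD before the stratum is added.
- g = 5: 5.06/225 = 2.2%; the standard error without the stratum is 1/√0.978, about 1% too large.
- g = 10: 20.25/225 = 9.0%; about 5% too large.
- g = 15: 45.6/225 = 20%; about 12% too large, but this g equals the whole planned SD.

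**Step 4, bias through diabetes.** Share with diabetes among completers = p(1−d₁) / [p(1−d₁) + (1−p)(1−d₀)], where p = 0.418 and d₁, d₀ are the dropout rates with and without diabetes. Bias = (share on dapagliflozin − share on placebo) × g.

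| Arm pattern | d₁ / d₀ | Overall loss | Share with diabetes |
|---|---|---|---|
| A | 30% / 13% | 20.1% | 0.2926/0.7989 = 0.366 |
| B | 20% / 20% | 20.0% | 0.418 |
| C | 10% / 27% | 19.9% | 0.3762/0.8011 = 0.470 |

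- Both arms follow A: difference 0, bias 0 for any g.
- Placebo A, dapagliflozin B: difference 0.052; bias 0.26 (g = 5), 0.52 (g = 10), 0.78 (g = 15) g/m².
- Placebo A, dapagliflozin C: difference 0.103; bias 0.52, 1.03, 1.55 g/m².

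The sign depends on which arm loses whom and on the direction of the covariate effect, so the bias could favour or oppose dapagliflozin.

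**Step 5, other patterns.** With 35% dropout among patients with low urine volume in one arm, 20% loss overall in each arm and no dependence in the other arm, the same formula gives 0.26 to 0.79 g/m². With 35% in one arm and 10% in the other it gives 0.44 to 1.32 g/m². The 35% versus 10% pattern applied to diabetes reaches 1.96 g/m².

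**Step 6, what this does to the test.** Type I error = Φ(−1.96 + b/SE) + Φ(−1.96 − b/SE). Power with bias b toward the null = Φ((7 − b)/SE − 1.96).
- b = 0.52 (0.23 SE): type I error about 5.6%; power falls from 87% to 82%.
- b = 1.55 (0.69 SE): type I error about 10.5%; power about 67%.

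**The case against.** The strongest reply is that the plan already handles this. It prespecifies imputation with exactly these four variables, pattern-mixture models for data missing not at random, and reporting of missingness by arm, so a bias of this kind should show up. That stands: no missing-data analysis is absent, and the point concerns only what the primary model contains. It does not remove the point, because a sensitivity analysis that disagrees does not replace the primary p-value, and the omitted stratum affects precision whatever the dropout.

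The size rests wholly on assumptions. The document reports no dropout pattern and no covariate effect. The milder case is 0.26 to 0.78 g/m², or 0.11 to 0.34 standard errors. The upper end needs opposite patterns in two blinded arms and an effect equal to the planned SD. This also stands.

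A reader might infer that the complete-case ANCOVA is valid only if dropout is unrelated to 6-month LVMI given arm and baseline LVMI. For the treatment contrast that is too strong. Equal dependence on a covariate in both arms leaves the contrast unbiased when the treatment effect does not vary with that covariate, as the first case in step 4 of the working shows. Nor does the analysis require data to be missing completely at random.

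A reader might also infer that imputation over all randomised patients should become primary. The documents do not support that as a clear gain: it would assign a 6-month LVMI to patients who died, and it adds only baseline information.

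Finally, the article is condensed, and an analysis plan not shown may name further covariates. If it does, saying so settles the point.

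**Conclusion.** The point holds in a limited form. As published, the primary model leaves out the stratification factor and three other baseline variables that the plan itself uses to predict missing outcomes. The precision cost is about 1% to 5% of the standard error for a stratum effect of 5 to 10 g/m². The possible bias is about 0.3 to 1.6 g/m² under the main illustration (4% to 22% of the 7 g/m² target), and about 2.0 g/m² under the most extreme pattern tried. It arises only if dropout depends on these variables differently by arm, or if dropout depends on them and they also modify the treatment effect. Nothing in the article shows that either has happened, so it would be wrong to conclude that the primary result is biased. The case for change is that the remedy is nearly free, not that the planned analysis is invalid.

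**What to change.** Before unblinding, specify the primary ANCOVA with treatment, baseline LVMI, urine-output stratum as randomised, age (form stated in advance), sex and diabetes status. Keep the model with baseline LVMI alone as a prespecified sensitivity analysis, and report both estimates. The urine stratum matters most, because it is a feature of the design; the other three follow from the imputation model.

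The cost is four degrees of freedom: 176 − 3 = 173 residual degrees of freedom become 169 (age entered linearly). No new data are needed. It is nevertheless a change to a published primary model after enrolment has closed, so it needs a dated, documented amendment with the reason given. If unblinding has already taken place, the adjusted model can only be reported as a labelled supplementary analysis.

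The change corrects only for loss explained by these baseline variables. It does not address death or deterioration after baseline, so the pattern-mixture models stay as planned. Main-effect terms also do not correct for a treatment effect that varies by stratum; the planned interaction analysis covers that question.
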